## Abstract

**Background:**

Scaling effective primary care innovations to benefit more people is of interest to decision makers. However, we know little about how promising innovations are being scaled “spontaneously,” that is, without deliberate guidance.

**Objective:**

We aim to observe, document, and analyze how, in real-life conditions, 1 primary care innovation spontaneously scales up across Quebec, Canada.

**Methods:**

We will conduct a participative study using a descriptive single-case study. It will be guided by the McLean and Gargani principles for scaling and reported according to the COREQ (Consolidated Criteria for Reporting Qualitative Research) guidelines. Informed by an integrated knowledge translation approach, our steering committee will include patient users throughout the project. Inspired by the Quebec College of Family Physician’s “Dragons’ Den” primary care program, we will identify a promising primary care innovation that is being or will be scaled spontaneously. We will interview the innovation team about their scaling experiences every month for 1 year. We will conduct interviews and focus groups with decision makers, health care providers, and end users in the innovation team and the target site about their experience of both scaling and receiving the scaled innovation and document meetings as nonparticipant observers. Interview transcripts and documentary data will be analyzed to (1) compare the spontaneous scaling plan and implementation with the McLean and Gargani principles for scaling and (2) determine how it was consistent with or diverged from the 4 McLean and Gargani guiding principles: justification, optimal scale, coordination, and dynamic evaluation.

**Results:**

This study was funded in March 2020 by the Canadian Institutes of Health Research. Recruitment began in November 2023 and data collection began in December 2023. Results are expected to be published in the first quarter of 2024.

**Conclusions:**

Our study will advance the science of scaling by providing practical evidence–based material about scaling health and social care innovations in real-world settings using the 4 guiding principles of McLean and Gargani.

**International Registered Report Identifier (IRRID):**

PRR1-10.2196/54855

## Introduction

The subject of scaling has long been present in various knowledge areas such as renewable energy sources [1], sustainability [2], and education [3]. Scaling is now rapidly gaining the attention of decision makers in health and social care, particularly in high-income countries [4]. In the literature and practice record, there are numerous means proposed for scaling innovations [5]. Many of these propose modifiers, such as scaling up or out and vertical or horizontal scaling, are used in an attempt to describe the different ways in which innovations are scaled or spread. ExpandNet, a World Health Organization–affiliated group, has produced several widely used practical guides on the topic and defines scaling up as an action that aims to increase the impacts of successfully tested innovations to benefit more people [6]. Thus, it is no surprise that alongside this World Health Organization practice–oriented initiative, scaling science is emerging as a distinct complement to applied or implementation science [7-9]. The term “scaling science” has a double meaning: the first referring to approaches to bringing innovations to optimal scale for the public good and the second referring to the critical and systematic (ie, scientific) study of these approaches to scaling [7,8].

Unfortunately, Canada is a country notorious for promising pilot projects that do not get scaled [10]. Explanations for this include the fact that Canada is comprised of multiple distinct health and social care systems [11]. In addition, the most effective scaling seems to occur in low- and middle-income countries, which may reduce the opportunities for decision makers from high-income countries to improve their knowledge and competencies in scaling [5]. Another potential explanation lies in the complexity of scaling health and social innovations [12,13] and the methodological traditions that prioritize testing with randomized controlled trials before scaling up [14,15]. This contributes to lengthening the scaling process, while decision makers are often focused on short-term impact. Finally, there is increasing pressure on high-income countries to reduce waste and implement effective innovations already scaled in low- and middle-income countries [16]. Now that high-income countries face a rapidly changing society with increasing resource constraints, effective scaling of beneficial innovations has become a high priority [17].

Most scaling occurs in the absence of scaling guidelines [5]. While there are attempts to establish rigorous and standardized guidelines, there is also a pressing need for studies that look at how scaling currently occurs on the ground when a promising or effective health care innovation is naturally or “spontaneously” expanded to reach a broader population. We adopted ExpandNet’s definition of spontaneous scaling as “diffusion of the innovation without deliberate guidance” [18]. The likelihood of spontaneous scaling is highest when the innovation effectively meets a clearly recognized need in a population or when a significant and urgent harmful event brings attention to the need to scale, for example, the COVID-19 pandemic [18]. Although the effectiveness of the innovation to be scaled should be demonstrated by its positive impacts on the public good, that is, it improves the well-being of individuals and populations through an increase in the quality of care [5,8], many experts and decision makers recognize that this is not always possible when facing a public health emergency [15,19]. Observation and analysis of spontaneous scaling are necessary to capture this process of adjusting plans and practice in real-life situations and will inform the knowledge base of scaling. Therefore, we aimed to observe, document, and analyze the spontaneous scaling (ie, that reflects the needs of a population but does not follow guidelines) of a promising primary care innovation within a specific health care context, compare it with the guiding principles of scaling described by McLean and Gargani [7-9], and make recommendations.

## Methods

### Overview of Study Design and Context

This study is a descriptive case study [20-22] adhering to the Rosenberg and Yate [23] recommendations for case study designs, which aim to comprehensively explore a particular case, including exploration of the phenomenon of interest and its contextual factors. Specifically, we define the case as the spontaneous process of scaling a promising primary care innovation within a specific health care context. The health care context is 2 large regional primary care organizations (an Integrated Health and Social Services Center [*Centre Intégré de Santé et de Services Sociaux*; CISSS] and an Integrated University Health and Social Services Center [*Centre Intégré Universitaire de Santé et de Services Sociaux*; CIUSSS]) within the Quebec health and social care services system. These 2 organizations are the administrative entities responsible for the delivery of health and social care services within their designated regions and for coordinating and integrating various facilities, such as hospitals, long-term care centers, rehabilitation centers, and community health centers.

### Case Study Approach

To gain insights into the real-life spontaneous scaling process of a promising innovation, we will delve into a specific case and draw broader conclusions about the phenomenon at conclusions. This research will also take an interpretative epistemological approach [24] to understand the context of the case from different perspectives. By using these approaches, we will shed light on the various factors and challenges associated with the scaling of spontaneous primary care innovations in real-world settings. We will report our findings using the COREQ (Consolidated Criteria for Reporting Qualitative Research) checklist [25].

### Scaling Framework

The documentation and analysis of the scaling process for this case study will be guided by a framework inspired by guiding principles proposed by McLean and Gargani [7-9]. This framework is based on a retrospective review of over 200 research and innovation projects funded by Canada’s International Development Research Centre. The choice to use the McLean and Gargani principles was influenced by three factors: (1) they allow for adaptability and flexibility throughout all phases of the scaling process, which is coherent with a spontaneous approach and with the real-life context of this study (ie, unexpected changes can be accommodated and plans adapted); (2) the guidelines apply an equity lens and emphasize the importance of ethics in assessing scaling impacts; and (3) the principles support our aim of focusing on the impacts of scaling on the public good, a focus that promotes placing the main emphasis on the end users in all scaling initiatives.

The 4 guiding principles for scaling impact described by McLean and Gargani [8,9] are justification, optimal scale, coordination, and dynamic evaluation. “Justification” addresses both ethical and technical issues. Before asking how to scale, one must ask why or whether to scale and about its technical feasibility. For example, does this web-based course for social workers have the necessary infrastructure to reach more professionals (technical justification)? What kind of impact on the public good will the course provide (ethical justification)? “Optimal scale” challenges the logic of “the more the merrier” and involves making informed decisions about choosing a scale that creates an optimal mix of magnitude, variety, sustainability, and equity [7]. This requires careful consideration of the potential benefits and risks and requires judgment in balancing desirable and undesirable impacts. For instance, if the course is scaled up to 1000 social workers but is only available temporarily, and only to those working in private settings, scale-up meets the magnitude goals but not the sustainability or equity goals. “Coordination” addresses relational issues; demands flexible articulation among the complex systems; and connects the diverse actors in the scaling process, such as the initiators, the enablers, the competitors, and the people affected by scaling. For example, coordination among those involved in identifying the need for the social workers’ course, those who developed the course, those who adapted and scaled it to further contexts, those who are evaluating it, those who are receiving the scaled-up version, and those who are receiving services from the newly trained social workers. For example, coordination in the case of the social workers' course would involve coordination among those who identified the need for the course, the course developers, those responsible for adapting and scaling it to diverse contexts, the evaluators assessing its effectiveness, and recipients of the scaled version. Coordination involves complexity, and this involves flexibility that requires an iterative process [8]. “Dynamic evaluation” addresses assessments in all phases of scaling: before, during, and after. Dynamic evaluation is not a linear before-after comparative assessment, but a constant application of evaluative thinking to check and adapt when necessary since scaling is a process that can change depending on the context of the site and innovation.

### Coproduction Approach and Project Governance

Following the integrated knowledge translation approach [26,27], this study embraces the active engagement of knowledge users as equal partners working alongside researchers in all research steps. Through coproduction [28,29], we aim to generate knowledge that is valuable and meaningful to all stakeholders involved in the research process.

To ensure effective project governance, the research team will establish a steering committee consisting of key stakeholders who will provide expert advice, recommendations, and feedback on questions as they arise. This committee will oversee and coordinate each stage of the study and focus on topics that directly impact the project. The committee members will include the project leader; study coordinator; coinvestigators (1 or 2); knowledge users (1 or 2); and end users, who may include citizen or patient partners (1 or 2). This diversity of stakeholders ensures inclusive representation throughout the project’s duration.

### Participants

#### Criteria for Choice of Innovation, Innovation Team, and Target Site

We will choose an innovation from a previous edition of the *Innovation Symposium*, a program organized by the Quebec College of Family Physicians inspired by the TV program “The Dragon’s Den” [30]. This event allows innovators, most of whom are from a clinical context and not from a research background, to pitch their promising innovations to clinical leaders and influential stakeholders (the Dragons) in Canada’s primary care ecosystem. If the Dragons consider the innovation promising, they will contribute toward accelerating its growth and scaling it. Based on our research team’s firsthand experience as attendees at previous symposiums (2017, 2019, and 2022), we will identify a spontaneous primary care innovation with considerable potential for scaling.

We will determine if the team is willing to participate in the project and, through a three-part questionnaire, whether (1) the innovation, (2) the innovation team, and (3) the context in which the innovation is embedded meet the following inclusion criteria based on our previous work [31-33] (Figure 1).

Inclusion criteria for the innovation: there is a spontaneous demand for scaling, the innovation aims to meet a demand for relevant primary care and services in the province of Quebec, the innovation has an epidemiological justification, the innovation is part of a health organization in Quebec, and the innovation has already been piloted and shown to be effective.Inclusion criteria for the innovation team: it has a committee or governance for the development and scaling of the innovation, it is part of a health organization in Quebec, it accepts that the research team participate as an observer in its strategic meetings, it agrees to nominate a person to be the coordinator responsible for the monthly and weekly follow-up with the members of the research team, the innovation team coordinator accepts the responsibility for connecting the research team with managers and health professionals in the target scaling setting, and the innovation team will be available during the research period (1 year) for monthly update meetings to respond to weekly ad hoc email requests from the research team on the innovation and the scaling process.Inclusion criteria for the target site: a specific geographical place is targeted to receive the innovation or there are professionals already using the innovation in the place where it is exposed who are not members of the innovation team, the plan for receiving the scaled innovation is embedded in a health organization in Quebec, an organizational structure is available for receiving the scaled innovation, and partners in the target site are in place to support the scaling plan.Inclusion criteria for individual participants: participants must be at least 18 years old; able to provide informed consent; able to actively participate, read, understand, and communicate in English or French; involved; in contact with or affected by the scaling initiative; and a decision maker in a health and social care organization, a health care provider, or a scaling expert working in the province of Quebec.

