#### Support for Scaling

The steering committee will establish a support network for the innovation team. Supporting organizations will be instructed to offer support and advice for scaling without providing a ready-made scaling plan. We will conduct semistructured interviews and focus groups, with the following four categories of interviewees: (1) decision makers from health and social care organizations (n=1-4), (2) health care providers (n=3-8), (3) members of the innovation team responsible for scaling (n=2), and (4) end users (n=2-4).

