#### Target Site

We intend to seek input from a range of decision makers (n=1-4), health care professionals (n=3-8), and end users (n=2-4) at the target site, as identified by the innovation team, regarding their firsthand experience with implementing the scaled innovation. We will conduct 1-hour semistructured interviews and focus groups (n=6-8). Participants in both interviews and focus groups will be asked about the innovation and their experience of scaling the health innovation, their view on the successful adaptation or not of the innovation, suggestions for improvement, potential factors influencing its implementation in their context, and possible complementary actions to be put into practice. One-hour individual structured interviews will be conducted face-to-face or on digital platforms (Teams [Microsoft Corp] or Zoom [Zoom Technologies Inc]) and adapted to accommodate the availability of participants. We will hold focus groups with the health care providers lasting 2 hours (maximum) outside office hours to reduce the impact on the services offered. Interviews will be conducted in English or French. One of the research team members with expertise in scaling and training in health care research innovation will conduct the interviews and focus groups. The interviews and focus groups will be recorded and transcribed, while an assistant moderator will be responsible for taking meeting notes during the interviews and focus group sessions. We will also participate as nonparticipant observers in some key meetings of the innovation team or training sessions given by the innovation team. During the observation periods, the research team will take observation notes about the meeting and the scaling process.

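### The individual inclusion criteria require a professional role, so as written they make ineligible end users whom the protocol plans to interview as a separate category

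*Protocol article*

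**What the plan says.** Under Criteria for Choice of Innovation, Innovation Team, and Target Site, the article lists what each individual participant must satisfy: adult age, capacity to consent, ability to take part in English or French, and being involved, "in contact with or affected by the scaling initiative". The list then closes with a role clause, joined by *and*: "a decision maker in a health and social care organization, a health care provider, or a scaling expert working in the province of Quebec".

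Support for Scaling names four categories of interviewee, with numbers: "1) decision makers from health and social care organizations (n=1-4", "2) health care providers (n=3-8", two members of the innovation team responsible for scaling, and "4) end users (n=2-4". The Target Site section repeats the last group as "end users (n=2-4) at the target site, as identified by the innovation team". The abstract also plans interviews and focus groups with end users, the Interview Guide section gives them a separate guide, and the Results section reports that this guide has been adapted.

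The Scaling Framework section gives, as one reason for choosing the McLean and Gargani principles, that they promote "placing the main emphasis on the end users in all scaling initiatives".

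**The concern.** Eligibility criteria are the operative screening rule. Here the rule names three roles, none of which describes a patient or citizen who simply receives or uses the innovation, while the sampling plan counts on such people as a category of their own. A recruiter who follows the rule cannot fill that category with them; one who fills it departs from the stated rule.

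What is at stake is the credibility of the end-user material. The framework was chosen partly for its attention to equity, ethics and the public good, and end-user interviews are the most direct source on those themes. If such interviews are missing, or were held with people whom the published criteria did not admit, the final report has to explain it.

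**Working it through.** No statistical figure is involved. The check sets the eligibility rule beside the sampling plan.

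**Step 1: structure of the rule.** The individual criteria form one list of requirements, with the role clause joined at the end by *and*. The three roles are alternatives to one another, but the clause as a whole is a further condition. Being affected by the scaling is therefore necessary but not sufficient.

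**Step 2: match the sampled categories to the roles.**

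| Category in Support for Scaling | Planned n | Named in the role clause? |
|---|---|---|
| Decision makers | 1-4 | Yes |
| Health care providers | 3-8 | Yes |
| Innovation-team members responsible for scaling | 2 | Not by name; eligible if they hold a listed role |
| End users | 2-4 | Not by name; eligible only if they hold a listed role |

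**Step 3: are end users a separate group?** Support for Scaling and Target Site both list them apart from decision makers and providers, and the Interview Guide section puts them on a different guide. Where the article illustrates the term, under Coproduction Approach and Project Governance and under Knowledge Mobilization, it mentions citizen or patient partners. Those two places concern the steering committee, so they illustrate the term without defining who will be interviewed.

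**Step 4: size of the affected category**, from the ranges in Support for Scaling.

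- Smallest total: 1 + 3 + 2 + 2 = 8. Largest total: 4 + 8 + 2 + 4 = 18.
- Without end users: 8 - 2 = 6 to 18 - 4 = 14.
- End-user share with all ranges at their lower ends: 2/8 = 25%. At their upper ends: 4/18 = 22%.
- Smallest possible share: 2/(4 + 8 + 2 + 2) = 2/16 = 12.5%. Largest: 4/(1 + 3 + 2 + 4) = 4/10 = 40%.

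These shares give the size of the category to which the inconsistency applies. They do not estimate how many people would be turned away.

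**The case against.** The best defence is that nobody would apply this clause against the rest of the plan. End users have a numbered category, a target-site number and a guide already adapted for them, and the criterion about being affected by the scaling describes them naturally. The sentence is also loosely drafted: a semicolon splits what is evidently a single criterion on involvement. All this makes an omission from a list of roles far likelier than a deliberate exclusion, and that stands. It does not remove the *and* before the role clause, so the contradiction remains.

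A reader might infer that the whole end-user category is lost. The documents do not support that. The end users to be interviewed are never defined; in the article's own illustration under Scaling Framework, the recipients of a scaled course are social workers, and the target-site criteria mention professionals already using the innovation. Some end users could hold a listed role.

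A reader might also infer that innovation-team members are excluded, or that the scaling expert role is an orphan because no interview category bears that name. Neither is shown. The role can plausibly cover team members responsible for scaling, and the article says that most innovators at the symposium come from a clinical context.

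Nor would the equity and public-good themes rest solely on those who deliver or manage the innovation. The plan also uses nonparticipant observation and documents, including postintervention feedback. These do not replace end-user interviews, but they are other sources.

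Finally, an article condenses a fuller protocol. That would excuse missing detail. It does not excuse an explicit rule that conflicts with the article's own sampling plan.

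**Conclusion.** The point holds as an internal inconsistency. As written, the individual inclusion criteria make ineligible any end user who is not also a decision maker, a health care provider or a scaling expert, while the abstract, Support for Scaling, Target Site, Interview Guide and Results sections all plan for end users as interviewees. The category concerned is 2 to 4 of 8 to 18 planned interviewees. How many of those 2 to 4 would fail the rule depends on who the end users of the chosen innovation are, which the article does not say: it could be all of them if they are patients or citizens without a listed role, and fewer if some are professionals.

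The conclusion rests on the ordinary reading of the list as cumulative. It does not imply an intention to exclude end users, and it says nothing about the wording of the full protocol, consent form or ethics submission, which are not shown.

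**What to change.** Reword the role clause so that it matches the four categories in Support for Scaling: keep decision maker and health care provider, and add *member of the innovation team responsible for scaling* and *end user of the innovation (eg, patient or citizen)*. State whether scaling expert is meant to cover the innovation-team category; if it means someone else, say where that person fits in the sampling plan.

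Then check the full protocol, consent form and ethics documents, and amend them only if they carry the same role clause. Recruitment began in November 2023 and data collection in December 2023, so the check should also establish which wording has been in use.

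The cost is one sentence in the criteria and a document check, with an ethics amendment only if the check shows that one is needed. No participants, interviews or analyses are added.
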